## Methods: monitoring

### Data monitoring

The principal investigator is responsible for maintaining the participant’s anonymity. The participants are informed of and consent to the research team accessing their medical records and registering personal health information of relevance to the study and study procedures, such as comorbidities and medication. The REDCap database can be accessed only by users specially assigned to the project, and login requires a personal username with two-factor authentication. All access to the database is fully logged and all actions are audited and can be traced. The principal investigator has full access to the database, except the randomization module which is fully shielded from all personnel except the implanters and device programmers.

### Adverse events

The principal investigator is responsible for continuously registering adverse events and side effects of any kind related to the TENS and ONS treatment. Data on all adverse events and side effects are registered and logged in the project-specific REDCap database. All side effects and adverse events are reported to the Central Denmark Region Committee on Health Research Ethics once a year, and collectively when the project is completed. Serious adverse events will be reported immediately to the Central Denmark Region Committee on Health Research Ethics.

In the blinded trial phase (burst ONS vs. placebo), none of the participants have access to the remote control for their ONS system, as this could potentially reveal the randomization of the participant. A clinical control after the postoperative grace period of 14 days is scheduled to ensure optimal conditions for program optimization. Should the participants suspect a problem related to the ONS system, direct contact can be made with the principal investigator, and the participant will then be seen by project staff who are trained in programming the system and who are unblinded for the randomization group. Where necessary, a clinical evaluation will be made by the ONS implanters at the Department of Neurosurgery, Aarhus University Hospital.

## Discussion

The effect of ONS on CCH has primarily been evaluated in case series and uncontrolled open-label studies [14–19], aside from a single large dose–response RCT [23]. In the 2023 European Academy of Neurology Guidelines on Cluster Headache [38] there is no recommendation for ONS due to the very low level of evidence. To our knowledge, the study presented here is the first randomized, blinded, placebo-controlled trial on ONS treatment for CCH; when completed, it should constitute a significant contribution to the evidence in the field.

Although little is known about burst stimulation for ONS, there are indications that this type of stimulation also has a preventive treatment effect in CCH patients. Because the participants do not perceive any sensation of stimulation, it enables the conduction of a blinded trial with burst ONS as the active comparator to an inactive placebo treatment.

Burst stimulation was introduced in 2010 and later marketed by neuromodulation device manufacturer Abbott as BurstDR. Subsequently, other manufacturers of neuromodulation systems have developed similar waveforms marketed under other burst labels. A difference in mechanism of action has been claimed [39], however, in this study we do not distinguish between the different variations of the burst waveforms.

The study design allows a comparison between burst ONS and placebo and enables a head-to-head comparison of the efficacy of burst and tonic ONS. In addition, by comparing the effect of treatment with TENS and tonic ONS, respectively, it is possible to evaluate whether the effect of TENS can be used as a feasible preoperative screening tool for ONS outcomes and can be used to select the most eligible candidates for implantation.

There is no official consensus about optimal stimulation settings in ONS for CCH. The study will provide important information about the efficacy of burst ONS and explore whether the addition of this stimulation paradigm might help improve future stimulation protocols.

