### Preoperative screening

Not all patients with CCH treated with ONS seem to experience sufficient if any, effect of ONS treatment [23]. Currently, no well-documented predictor for ONS outcome is known. Because of the invasive nature of the treatment, and the fact that ONS is characterized by high initial device costs, it would be favorable to have a reliable screening tool to help select the best candidates for implantation and avoid operating on patients who are unlikely to benefit from the ONS treatment.

It has been investigated if a previous good clinical response to interim treatment with prednisolone and/or a local anesthetic injected around the GON (i.e., a GON block) could predict ONS outcome, but without convincing results [27, 28]. Also, no specific clinical phenotypes that can distinguish which CCH patients are most likely treatment responders from non-responders have yet been identified.

In a small study, it has been suggested that non-invasive external transcutaneous electrical nerve stimulation (TENS) of the GON could be a possible predictor for ONS outcome [29], but it remains to be systematically explored whether TENS is a feasible preoperative screening tool.

The purpose of this study is to validate the efficacy and safety of ONS as a treatment for CCH and to explore whether burst ONS is as effective as headache attack prevention as conventional tonic ONS. In addition, we wish to investigate whether TENS of the greater occipital nerves (GON) can be used as a predictor of the effect of surgical treatment with ONS for CCH.

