#### Burst ONS

Burst stimulation is a stimulation paradigm devised to mimic the natural firing pattern of neurons by delivering electrical impulses in bursts (short trains separated by a gap). These impulses are delivered in sub-sensory amplitudes resulting in a paresthesia-free stimulation. The parameters for burst ONS (“MicroBurst”, Boston Scientific) are set with an intra-burst frequency of 450 Hz (six pulses), an inter-burst frequency of 40 Hz, and a pulse width of 300 μs [30]. Stimulation amplitude is set to 50% of the detection threshold.

Participants allocated to the burst ONS group receive this stimulation continuously throughout the 12-week blinded trial phase.

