#### Tonic ONS

In conventional tonic stimulation, the electrical impulses are delivered as regular biphasic square waves. All participants cross over to open-label tonic ONS as the final phase of the trial regardless of allocation group during the blinded part of the trial. A personal remote control allows the participants to change between three different pre-set stimulation programs with frequencies of 10, 30, and 100 Hz, respectively. Pulse width (250–500 µs) and configuration (polarity and activation) of the eight contacts on the linear lead are adjusted to achieve the best possible occipital paresthesia. The participants’ individual perception and comfort thresholds determine the amplitudes and can be controlled using the remote control. The participants are encouraged to use the stimulation continuously but are allowed intermittent use if preferred.

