**Secondary endpoints**
1. Participant’s assessment of treatment effect evaluated by PGIC-score
2. Treatment efficacy of burst versus tonic ONS as a preventive treatment for chronic cluster headache
3. Feasibility of TENS as a predictor for the outcome of ONS treatment
4. 30% reduction in pain intensity
5. Quality of life as evaluated with the EuroQoL-5D questionnaire
6. Reduction in background headache
7. Self-reported sleep quality
8. Symptoms of anxiety and depression as evaluated by HADS

*TENS* Transcutaneous electrical nerve stimulation, *ONS* Occipital nerve stimulation, *PGIC* Patient's global impression of change, *HADS* Hospital anxiety, and depression scale, *EuroQoL-5D* European Quality of Life – 5 Dimensions

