## Methods: assignment of interventions

### Randomization and blinding

After the 14-day grace period following ONS implantation, the ONS systems will be programmed and the participants will be allocated 1:1 in the two study groups (burst ONS or placebo). The allocation is conducted by block randomization with blocks of random size between four and eight, using a specially designed automated electronic randomization tool. The allocation tables for the randomization are inaccessible to the investigators and other staff involved in the project.

The randomization is performed by the implanter or the project nurse who is responsible for the programming of the ONS systems. These personnel are unblinded throughout the entire trial and are therefore able to handle any ONS-related events during the blinded trial phase without mitigating the blinding. Unblinded personnel will not have any role in data collection, management, and analysis.

The participants are blinded to their allocation group. The principal investigator and other study personnel who perform the evaluation of outcome parameters, are blinded to the allocation group as well, and will not have access to the randomization tool in the project database. Blinding is maintained until all participants have completed the final trial phase.

The IPGs used in the study are non-rechargeable units to ensure that a lack of need for recharging does not unblind the participants. In addition to this, to avoid accidental unblinding, the participants will not have the remote controls to the ONS system during the blinded trial phase, since the display would reveal if stimulation is on. Importantly, when treated with burst stimulation, participants should not have any sensation of stimulation and, hence will not need to adjust the stimulation amplitude. The postoperative 14-day grace period ensures accurate programming, which in our experience limits the need for stimulation adjustments within the 12 weeks of blinded trial to an absolute minimum. If needed, patients can directly contact the principal investigator. Should the participants get a sensation of stimulation during the blinded trial phase, unblinded personnel can adjust the stimulation settings if necessary.

When crossing over to the open-label tonic ONS trial phase, all participants are equipped with a remote control.

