### Statistical analysis

Statistical analysis will be conducted by the principal investigator and a statistician blinded for treatment allocation only after follow-up for all participants is completed. No interim analysis will be performed.

Characteristics of the patients will be presented using descriptive statistics to assess if balanced groups were obtained after randomization. The primary analysis will be conducted according to the intention-to-treat principle to avoid introducing bias. In a secondary analysis, a per-protocol analysis will be performed.

The primary outcome is a 30% reduction in attack frequency with TENS and ONS treatment compared to baseline. Relative change in attack frequency (in percent) will be analyzed using the Wilcoxon signed-rank test for paired variables, comparing the baseline data with data from the TENS trial and the trial with burst and tonic ONS, respectively. Because the changes in attack frequency are expectedly skewed [23], a non-parametric test will be applied. In cases with a minimum 30% reduction in attack frequency, sub-analyses will be made to group the treatment responders after relevant cutoffs.

Analysis of the secondary outcomes will be conducted according to the same principle, comparing data from each of the trial phases to baseline using a parametric or non-parametric test for paired variables, depending on the data distribution.

The feasibility of TENS as a predictor for ONS outcome will be evaluated by determining the sensitivity and specificity and calculating the predictive values.

Statistical data analysis will be performed using Stata 17.0 (StataCorp, College Station, USA-TX).

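### Burst versus tonic ONS is a secondary endpoint, but the stated method only tests each phase against baseline; the fixed order and open-label tonic phase also make head-to-head too strong a description

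*Protocol article*

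**What the plan says.** Four parts of the protocol article bear on this point.

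- **Aim and endpoint.** The study purpose, at the end of Preoperative screening, includes to "explore whether burst ONS is as effective as headache attack prevention as conventional tonic ONS". Table 4 lists as secondary endpoint 2: "Treatment efficacy of burst versus tonic ONS as a preventive treatment for chronic cluster headache".
- **Claim.** The Discussion says the design "enables a head-to-head comparison of the efficacy of burst and tonic ONS". The abstract makes a similar statement without the head-to-head label.
- **Method.** Under Statistical analysis, attack frequency is tested with the Wilcoxon signed-rank test, "comparing the baseline data with data from the TENS trial and the trial with burst and tonic ONS, respectively". Secondary outcomes follow the same principle, "comparing data from each of the trial phases to baseline using a parametric or non-parametric test for paired variables". The Outcome measures section also describes data from each phase as being compared with baseline.
- **Design.** Randomisation is 1:1 to burst or placebo. On burst: "Participants allocated to the burst ONS group receive this stimulation continuously throughout the 12-week blinded trial phase". On tonic: "All participants cross over to open-label tonic ONS as the final phase of the trial regardless of allocation group".

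**The concern.** A method is stated for the secondary outcomes, and for endpoint 2 it does not answer the question. Followed exactly, it gives one p-value for burst against baseline and another for tonic against baseline. Neither estimates a difference between the two waveforms. The tests also have unequal power, because one uses about 20 patients and the other about 40.

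The design adds a limit that no analysis removes. Neither the waveform (burst or tonic) nor its order is randomised. Tonic always comes second, is open-label and is adjusted by the patient with a remote control, whereas burst is blinded and given without one. No washout between the phases is described, and reduction of preventive medication is allowed during the trial. A difference between the phases therefore mixes waveform with period, carry-over, expectation and medication change.

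At stake is what the paper can say about burst relative to tonic. Two baseline tests could be taken to show that tonic works and burst does not, or that both work equally well, when the data establish neither.

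**Working it through.** **Inputs from the article.** 40 patients, 20 per arm; burst in one arm for 12 weeks; tonic in everyone for the final 12 weeks; four weeks of baseline; signed-rank test on percent change; at least 15 attacks per month to be eligible. The article gives no planning figure for burst versus tonic to reproduce: its sample size concerns burst versus placebo responders. It also gives no SD, no correlation between phases and no margin, so those below are assumptions shown as ranges.

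**Step 1. What the stated tests do when the waveforms are equal.** Simulation, 1,500 trials per setting. True rate ratio to baseline is 0.7 in both phases. Each patient-phase rate carries independent log-normal noise with the log-SD shown. The burst test uses 20 patients; the tonic test uses all 40, and the 20 burst patients have the same baseline value in both tests. The second model adds Poisson count noise at an assumed 30 attacks per four weeks.

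| Phase log-SD | Tonic significant, burst not (no count noise) | Reverse | Tonic significant, burst not (Poisson counts) | Reverse |
|---|---|---|---|---|
| 0.2 | 0.2% | 0% | 8% | 0.1% |
| 0.3 | 15% | 0.2% | 29% | 3% |
| 0.4 | 36% | 5% | 38% | 8% |

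Other runs of the same form agree within a few points. In round terms the misleading pattern appears in 0-10%, 15-30% and about 35% of trials. It leans towards tonic because the tonic test has twice the patients.

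**Step 2. What they do when the waveforms differ.** With normally distributed changes and tonic truly twice as effective (mean change 1.4 SD against 0.7 SD), both tests were significant in 83% of simulated trials. Two significant results therefore say little about equality.

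**Step 3. What a direct contrast would give.** Let d be each burst-arm patient's log ratio of tonic-phase to burst-phase attack rate. The 95% CI is the estimated ratio divided and multiplied by

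factor = exp(t(19; 0.975) × SD(d) / √20), with t = 2.093.

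If each phase has independent log-SD s, then SD(d) = √2 × s, which is 0.28 for s = 0.2 and 0.57 for s = 0.4. Values up to 0.8 allow for more variation.

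| Assumed SD(d) | Exponent | Factor | CI if the estimate were exactly 1 |
|---|---|---|---|
| 0.28 | 2.093 × 0.28 / 4.472 = 0.131 | 1.14 | 0.88 to 1.14 |
| 0.45 | 0.211 | 1.23 | 0.81 to 1.23 |
| 0.60 | 0.281 | 1.32 | 0.76 to 1.32 |
| 0.80 | 0.374 | 1.45 | 0.69 to 1.45 |

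On the responder scale, with no true difference and a proportion ψ of patients who respond to one waveform only, the half-width is 1.96 × √(ψ/20): 14 percentage points at ψ = 0.1 and 31 at ψ = 0.5.

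**Step 4. What the direct contrast cannot remove.** The placebo arm goes from a switched-off device to tonic. Comparing tonic-phase rates between the randomised arms therefore shows whether earlier burst left an effect, with at most 20 patients per arm and so with low power. It does not separate waveform from period, or blinded from open-label use.

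**The case against.** The strongest case on the other side is that the Discussion describes what the design makes possible and does not announce a test. Burst-arm patients have 12 weeks of each waveform on the same weekly registration, so a within-patient contrast exists. This stands. A reader might infer that the two analyses use unrelated patients, or that no comparison can be made at all; the documents do not support either reading, because the burst patients are a subset of the tonic patients.

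A reader might also infer that the trial plans to treat a non-significant difference as proof of equal efficacy. Nothing in the article says so. The aim is worded as exploratory, and endpoint 2 is one of eight secondary endpoints. What can be said is only that no margin is set, so such a conclusion would have no basis.

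It is equally tempting to say that tonic will look better because its sample is doubled. Doubling the number lowers the p-value and narrows the interval; it does not enlarge the median change or the responder rate.

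On confounding, the open-label tonic phase is disclosed, and the Background explains that paresthesia hinders blinding. The placebo arm also allows some check on carry-over. These points soften the criticism of the design but not the wording of the claim.

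Finally, an article condenses, and an unseen analysis plan may contain the missing contrast. Against that, the article states a method for the secondary outcomes and gives the predictive value of transcutaneous stimulation (TENS) a method of its own, while burst versus tonic is left under the baseline rule. That is a method that does not fit its endpoint, not an omitted detail. An analysis plan could supply the contrast, but it could not change the order or the masking.

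**Conclusion.** The point holds. The method stated for secondary endpoint 2 contains no burst-tonic contrast, and head-to-head overstates what a fixed-order comparison with an open-label second phase can show.

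The chance of a misleading split between the two tests depends heavily on assumed variation: negligible to about 10% at a phase log-SD of 0.2, and about 35% at 0.4. The direction is firm; the low end depends on the noise model. The precision of a direct estimate likewise rests on assumed SDs and on all 20 burst patients contributing both phases.

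The matter concerns a secondary, exploratory aim and leaves the randomised burst-placebo comparison untouched. It is still worth correcting, because the article says analysis starts only after all follow-up, with no interim analysis, so the change can be made before results are seen.

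**What to change.** 1. For endpoint 2, replace the baseline rule with a direct estimate in the burst-allocated arm only: the within-patient ratio of tonic-phase to burst-phase attack rate, with a 95% CI.
2. Compare tonic-phase attack rates between the two randomised arms as a carry-over check, and state that its power is low.
3. Label the result exploratory and confounded by fixed order and open-label tonic.
4. In the Discussion, replace the head-to-head wording with a description of an exploratory within-patient comparison in one arm.
5. State that no conclusion of equal efficacy will be drawn, since no margin is set.

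Treatment, visits and data collection do not change. The cost is a little more analysis and a weaker claim about burst relative to tonic.

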## Data Availability

All data is stored in the REDCap database system which can only be accessed by the primary investigator and study group. The full dataset will not be made available as further analyses may be performed including long-term follow-up analyses.

## Abbreviations

CCH: Chronic cluster headache
GON: Greater occipital nerve
HADS: Hospital anxiety and depression scale
IPG: Implantable pulse generator
NRS: Numerical rating scale
ONS: Occipital nerve stimulation
PGIC: Patient's global impression of change
TENS: Transcutaneous electrical nerve stimulation
